### Plans to give access to the full protocol, participant-level data, and statistical code {31c}

Data will be available for researches at the Center for Psychological Treatment of Children and Adolescents and researches from the Centre for Digital Psychiatry. They will have access to the study protocol, the statistical analysis plan, informed consent form, and analytical code.

Data will be stored on a server located in the Region of Southern Denmark. When the study is completed, the data will be transferred to The Danish National Archives. Data is available upon reasonable request. Restrictions apply to the availability of data and approval is needed from Danish Data Protection Agency and/or The Danish National Archives.

## Oversight and monitoring

### Composition of the coordinating center and trial steering committee {5d}

CEDIP is responsible for recruiting participants, delivering the program, and managing the database and research data as described in this protocol.

The research team will work as the trial steering committee, comprising members from both CEBU and CEDIP. They will hold meetings every third week for 1 h to oversee the trial’s day-to-day operations, monitor progress, and provide supervision.

The data managing team consists of one data manager from Open Patient Data Explorative Network (OPEN) collaborating with one data manager from CEDIP. The data managing team is in continuous contact with the research team.

### Composition of the data monitoring committee, its role and reporting structure {21a}

A data monitoring committee will be established, consisting of clinicians working on the project, the project data manager, and two PhD students. The committee’s role is to ensure data quality and monitor potential negative effects of participation in the study.

It’s important to note that this committee is not independent from the sponsor, as this study is internally funded. However, the data manager, who is connected to another hospital unit, is tasked with ensuring proper data management across the hospital and thus has no competing interests in the project.

### Adverse event reporting and harms {22}

Another committee, comprising clinicians working on the project and members of the research team, will be established to monitor individual risks on a case-to-case basis. This committee will oversee screening for depression and suicidality using S-MFQ scores, and anxiety symptom severity using CAS-8. Screening will occur daily, with exceptions for holidays and weekends.

Additional negative effects will be assessed through the NEQ after the adolescent have completed 14 weeks of treatment. If any risks or harms are detected, the committee will report to the assigned clinician. It will then be the clinician’s responsibility to contact the participant, and/or their legal guardians to investigate if the participant needs additional help. All adverse events will be recorded in the trials database.

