#### iCBT with on-demand feedback

Participants in the on-demand feedback iCBT condition will not receive any planned contact with the therapist. However, they will have the option to contact the therapist through messages within the program and receive asynchronous support.

In both treatment conditions, the therapist may spend a maximum of 15 min giving feedback per week. While we have advised therapists to adhere to this standard time used per participant in The Internet psychiatry, we cannot fully ensure adherence to this rule as it is up to the discretion of each therapist. Since there is no evidence on what amount of therapist support is sufficient for adolescents, the allowed time spent giving feedback will not differ between the two conditions. Participant depression and suicidality will also be continuously monitored in both intervention conditions using in-session questionnaires (see section “Plans for assessment and collection of outcomes {18a}”).

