### Criteria for discontinuing or modifying allocated interventions {11b}

If an adolescent shows an increase in co-morbid depressive symptoms above the cutoff for clinical depression, or if they show signs of suicidal ideation, the clinician will contact both the participant and their legal guardians to discuss whether the participant should be discontinued from the study and receive help finding other treatment if needed. The clinician may contact the participants up to three times during the trial to investigate depression or suicidal ideation. If the participant shows increase in depressive symptoms or exhibits suicidal ideation for the third time during the treatment, the purpose of the contacts will be to discontinue the participant from the study and help them find other treatment if needed.

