#### Secondary outcomes

The secondary outcomes consists of point differences in anxiety diagnosis and severity measured by clinician-review Youth Online Diagnostic Assessment-Child and Parent Versions (YODA) [48]. YODA is an online diagnostic assessment tool that assesses DSM-5 anxiety disorders and specific phobias based on the *Anxiety and Related Disorders Interview Schedule for DSM-5*, which is considered the golden standard [49]. The YODA uses yes/no responses to closed-ended questions, as well as open-ended questions that require written descriptions of cognitions, behaviors and impact on functioning [48]. The YODA is completed separately by the adolescent and the parents, and a clinical psychologist trained in the assessment of adolescent anxiety disorders then reviews and evaluates the responses to determine the diagnosis and symptom severity.

Point differences in anxiety symptoms interference on daily life measured by the self- and parent-reported questionnaire Child Anxiety Life Interference Scale (CALIS) [46]. CALIS [50] is used to measure the impact of youth anxiety on various areas of life functioning such as school, extracurricular activities, family life and friendships. The impact is evaluated separately by adolescents and their parents. In addition, parents rate the degree of impact on their own lives. CALIS has shown satisfactory internal consistency and moderate test-retest reliability [50].

Point differences in depressive symptoms are measured by The mood and Feelings Questionnaire (MFQ) [51]. MFQ is used to screen for depression in youth, both in epidemiological samples and in clinical samples, it is recommended as a self-report screening tool in secondary care [51]. The MFQ is completed separately by the adolescent and a parent. The MFQ has been validated in a Danish population sample of adolescents and shown excellent internal consistency [52].

Point differences in Quality of life is measured by EuroQol-5 Dimension Youth (EQ-5D-5L) [52], a 5-item self-report questionnaire assessing quality of life and self-rated health. The items cover five domains: mobility, self-care, usual activities, pain/discomfort, and anxiety and depression [53].

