#### Weekly outcomes

The 8-item Children’s Anxiety Scale (CAS-8) [61]. The CAS-8 is a short version of the SCAS containing 8 items. I has shown acceptable psychometric properties, with good reliability [61].

The Short Mood and Feelings questionnaire (S-MFQ) [62]. The S-MFQ is a short version of MFQ, at shows high accuracy for discriminating MDD cases from non-cases [63].

Sociodemographic measures will be gathered on parents regarding age, level of education, job status, civil status, gender, and primary caregiver in case of single parents. For the adolescents, information will be gathered regarding age and gender.

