## Assignment of interventions: Blinding

### Who will be blinded {17a}

Given the nature of the study examining the effectiveness of a novel format of psychotherapy and the examination of difference in therapist support, blinding participants and clinicians is not possible. Additionally, the research team actively engages in day-to-day project operations, including the screening for suicidality, and therefore, the research team is not blinded.

However, to mitigate bias, the trial results will be analyzed using pseudo-anonymized data. This means that only the ID numbers will appear on the data sheet, aiming to achieve as close to assessor blinding as possible within the research design.

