## Data collection and management

### Plans for assessment and collection of outcomes {18a}

All questionnaire measures will be collected using REDCap [38, 39]. Participants will receive automatic reminders sent after 4 and 8 days. If participants have not completed the questionnaires after receiving reminders, a member of the research team will contact them by phone in an attempt to re-engage them.

For post-treatment and follow-up measures, contact will be attempted a maximum of 3 times in total at different time points to prompt completion.

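### Suicidality screening during treatment rests on S-MFQ scores, which the protocol supports only for depression, although suicidal ideation is its own trigger for clinician contact

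*Protocol article*

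**What the plan says.** Four parts of the protocol article bear on this.

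- **Trigger.** Criteria for discontinuing or modifying allocated interventions {11b} has the clinician contact the family when depressive symptoms rise "above the cutoff for clinical depression, or if they show signs of suicidal ideation". At the third occurrence of either, the purpose of the contact becomes discontinuation and help in finding other treatment.
- **Screen.** Adverse event reporting and harms {22} sets up a committee that oversees "screening for depression and suicidality using S-MFQ scores", with the CAS-8 for anxiety severity. Scores are looked at daily except on weekends and holidays.
- **Description of the instrument.** Weekly outcomes says: "The S-MFQ is a short version of MFQ, at shows high accuracy for discriminating MDD cases from non-cases". Secondary outcomes says of the full scale: "MFQ is used to screen for depression in youth".
- **Other mentions.** The section on iCBT with on-demand feedback states: "Participant depression and suicidality will also be continuously monitored in both intervention conditions using in-session questionnaires", and refers to section {18a} for details. Who will be blinded {17a} lists, among the research team's daily tasks, "including the screening for suicidality". Neither place names a measure.

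**The concern.** The participants are 12 to 17 years old and have anxiety disorders, and the protocol itself treats suicidal ideation as a reason to act. A trigger works only if something feeds it. The only input named for suicidality is a score from a depression scale, and the only property the protocol gives that scale is separating depressed from non-depressed cases. An adolescent who reports ideation while scoring low overall meets the contact rule, but the protocol does not show how the named screen would bring this to the clinician. What is at stake is participant safety during the 14 weeks of treatment. No estimate or test is affected.

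**Working it through.** No figure in the protocol needs reproducing here. The check sets the sections side by side.

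1. **Are there two triggers or one?** Section {11b} joins the depression cutoff and signs of ideation with an *or*. Ideation below the cutoff is therefore enough for contact. The two share one rule and one limit of three contacts, so no separate count of ideation episodes is needed.

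2. **What feeds the ideation trigger?** Section {22} names S-MFQ scores. The shown text names no other suicidality instrument, item or threshold.

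3. **What does the protocol claim for those scores?** Weekly outcomes and Secondary outcomes claim discrimination of, and screening for, depression. Neither mentions ideation. A score that sorts depression cases well does not by that fact identify ideation in someone below the cutoff.

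4. **Does the cross-reference fill the gap?** The monitoring sentence in the on-demand section leads to {18a}. That section opens with "All questionnaire measures will be collected using REDCap" and goes on to reminders and contact attempts. It names no suicidality measure, so the reference leads nowhere on this point.

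5. **Do other safeguards cover ideation that arises during treatment?**
   - The exclusion of current ideation (Eligibility criteria {10}) and the psychologist's interview (Participant timeline {13}) come before randomisation.
   - Review on working days makes the response faster but adds no content, since the scores reviewed are the same.
   - The NEQ and the final video call come after the 14 weeks.
   - Outreach under {18b} is set off by more than 10 days of inactivity, which an adolescent who keeps logging in does not reach.
   - A parent takes part, but no parent report of ideation is described as an input to the screening.

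   These lower the risk. None is a systematic measure of ideation during treatment.

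6. **Can the size be computed?** No. The missed share would need the S-MFQ items, the cutoff value and the joint distribution of ideation and score. The protocol gives none of them.

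**The case against.** The strongest reply is that the gap is read into missing detail. A journal article does not list questionnaire items or alert rules. Table 3 (the participant timeline) is not shown in the text available, there is supplementary material, and Frequency and plans for auditing trial conduct {23} refers to a field guidebook with step-by-step instructions. Any of these could hold an ideation item. The harms section also says scores without saying total score, and the *or* in {11b} fits a separate ideation signal as well as it fits a gap.

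Much of this stands. It rules out saying that ideation is being missed. It does not remove the point, because the article is not silent. It names a method for screening suicidality, that method is supported in the text only for depression, and the reference meant to explain the monitoring leads to no measure.

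Three stronger readings are tempting, and the documents support none of them.

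- *The screen fails for adolescents below the cutoff.* The item content and any item-level review are not shown, so failure cannot be inferred.
- *The on-demand arm is the exposed one.* Its participants "will not receive any planned contact with the therapist", while the other iCBT arm gets weekly written feedback. But the questionnaire monitoring is the same in both iCBT arms, participants in both can write to the therapist, and the weekly feedback concerns assignments and is not described as a check for ideation. The point therefore applies to both arms alike.
- *The size is 56 × 14 = 784 participant-weeks.* That is the planned treatment time of the on-demand arm. It is not a count of missed ideation or of harm.

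**Conclusion.** The point holds as a safety risk in the plan as written. The named screen does not secure the ideation trigger for an adolescent with a low S-MFQ score, in either iCBT arm, and the cross-reference to {18a} leads to no suicidality measure. No magnitude can be given. Power, error rates and the comparison of arms are not affected, and nothing here suggests bias between arms.

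The conclusion rests on the protocol's own description of the S-MFQ and on the absence of any other suicidality measure in the text shown. If an ideation item is already administered and reviewed regardless of the total, the point reduces to one of wording. The change is still worth making, because the text would then state the route on which the contact rule depends.

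**What to change.** In Adverse event reporting and harms {22}, designate one suicidal-ideation item in the weekly in-session questionnaire for both iCBT arms, or add one if none is administered. State that any positive answer alerts the committee whatever the S-MFQ total. In the on-demand section, point the monitoring sentence to {22} instead of {18a}. What the clinician does after an alert stays as in {11b}, including the three-contact rule.

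This is a cheap improvement that fits the existing working-day review. The cost is at most one extra weekly item, some false alerts for clinicians to follow up, and an ethics notification. If such an item is already in use, only the wording changes.

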### Frequency and plans for auditing trial conduct {23}

The project will be closely monitored by the Principal clinical investigator, who is internal to the project. Every 6 months, the Principal Clinical Investigator will conduct an inspection to ensure compliance with the study protocol and the guidelines for Good Clinical Practice [67].

To ensure adherence to the study protocol, all researchers involved in the project must commit to following a field guidebook with detailed instructions for each step of the study.

Additionally, the Regional Committees on Health Research Ethics for southern Denmark has the authority to inspect the project during the trial period to ensure compliance with the approved ethical protocol.

### Plans for communicating important protocol amendments to relevant parties (e.g., trial participants, ethical committees) {25}

Having completed a feasibility trial resulting in adaptations and amendments to the protocol approved by the ethical committee, we anticipate minimal further amendments. However, if significant amendments are necessary, we will promptly communicate them to the National Committees on Health Research Ethics of Denmark for approval.

Similarly, any important amendments that affect participant participation or their experience in the trial will be promptly communicated to participants, no later than 1 week after approval and implementation. In cases of major amendments, the participants will be contacted by phone by a member of the research team.

Additionally, information regarding amendment will be published on the CoolMinds.dk website. All relevant parties will also be informed by mail by the research team.

### Dissemination plans {31a}

The results of the project will be submitted to high-impact international and peer-reviewed journals under open access, and presented at national and international conferences. Additionally, the research team will organize public lectures, courses, and workshops to disseminate understanding of anxiety in youth and treatment options among professionals and the general public.

A layman summary of the results will be composed and forwarded to participants who have expressed interest, as well as published on the CoolMinds website. Currently, six scientific articles are planned to be submitted based on the results from the project, which will be part of two PhD dissertations.

The following six articles are planned:Paper 1: A systematic review of research on iCBT and the use of support and booster sessionsPaper 2: Predictor analysis of treatment outcomePaper 3: Results from the feasibility trialPaper 4: Results from the RCTPaper 5: Trajectory of change multiple single case descriptionsPaper 6: Network analysis of symptoms, severity, and change from pre- to post-treatment.

## Discussion

The present study aims to investigate the clinical effectiveness of the iCBT intervention CoolMinds when delivered with either planned therapist feedback or on-demand therapist feedback. Additionally, the study aims to examine the effects of providing one booster session 10 weeks after completion of the treatment program. The online format may help overcome barriers for adolescents seeking anxiety treatment without compromising the effectiveness of traditional CBT.

A strength of the study lies in the identical content of the CoolMinds intervention in both active conditions, allowing for a direct comparison of the therapist support levels in iCBT for adolescents. Furthermore, a feasibility trial has already been conducted, mitigating concerns regarding technical problems and operational issues. However, initial low recruitment numbers and potential high dropout rates may delay the study and challenge the examination of booster session effects. Additionally, the study’s reliance on a small number of clinicians leaves it vulnerable to long-term absences or discontinuation.

This study will contribute to the existing literature with knowledge on the effectiveness of iCBT in adolescents with anxiety when comparing therapist feedback levels and examining the effects of booster sessions. The results aim to improve the accessibility of evidence-based treatment for adolescents with anxiety.

## Trial status

Version number 1.

Recruitment began September 1st 2023. The first participants were included and started treatment on October 18th.

Recruitment is approximated to end June 2025.

## Data Availability

Data will be available for researches internal to the project at Aarhus University, Center for Psychological treatment of Children and Adolescents and researchers from Center for Digital Psychiatry. They will have access to the study protocol, statistical analysis plan, informed consent form, and analytical code.

## Abbreviations

CBT: Cognitive Behavioral Therapy
CEBU: Center for Psychological Treatment of Children and Adolescents
CEDIP: Center for Digital Psychiatry
DSM-V: Diagnostic and Statistical Manual of Mental Diseases V
iCBT: Internet-based cognitive behavioral therapy
ICC: Intraclass coefficient
GP: General Practitioner
NGO: Non-governmental organization
OCD: Obsessive compulsive disorder
OPEN: Open Patient data Explorative Network
RCT: Randomized controlled trial
SCAS: Spence Child Anxiety Scale
YODA: Youth Online Diagnostic Assessment
S-MFQ: The Short Mood and Feelings questionnaire
CAS-8: The 8-item Children’s Anxiety Scale
DSM-5: Diagnostic and Statistical Manual of Mental Disorders
ADHD: Attention deficit hyperactivity disorder
ADD: Attention deficit disorder
CALIS-C: Child Anxiety Life Interference Scale-Children
CALIS-P: Child Anxiety Life Interference Scale-Parent
MFQ-C: The Mood and Feelings Questionnaire-Children
MFQ-P: The Mood and Feelings Questionnaire-Parent
EQ-5D-5L: EuroQol-5 Dimension Youth
NEQ: Negative Effects Questionnaire
SUS: Systems Usability Scale
WAI-TECH-SF: Working Alliance Inventory applied to Internet
WAI-SF: Working Alliance Inventory – Short Form
ICC: Intraclass correlation coefficient
ID: Identity
